## Abstract

**Background:**

The aim of this study is to evaluate the performance of the first certified regional trauma network in Germany, the Trauma Network Eastern Bavaria (TNO) addressing the following specific research questions: Do standard and maximum care facilities produce comparable (risk-adjusted) levels of patient outcome? Does TNO outperform reference data provided by the German Trauma Register 2008? Does TNO comply with selected benchmarks derived from the S3 practice guideline? Which barriers and facilitators can be identified in the health care delivery processes for polytrauma patients?

**Method/design:**

The design is based on a prospective multicenter cohort study comparing two cohorts of polytrauma patients: those treated in maximum care facilities and those treated in standard care facilities. Patient recruitment will take place in the 25 TNO clinics. It is estimated that *n* = 1.100 patients will be assessed for eligibility within a two-year period and *n* = 800 will be included into the study and analysed.

Main outcome measures include the TraumaRegisterQM form, which has been implemented in the clinical routine since 2009 and is filled in via a web-based data management system in participating hospitals on a mandatory basis. Furthermore, patient-reported outcome is assessed using the EQ-5D at 6, 12 and 24 months after trauma.

Comparisons will be drawn between the two cohorts. Further standards of comparisons are secondary data derived from German Trauma Registry as well as benchmarks from German S3 guideline on polytrauma.

The qualitative part of the study will be based on semi-standardized interviews and focus group discussions with health care providers within TNO. The goal of the qualitative analysis is to elucidate which facilitating and inhibiting forces influence cooperation and performance within the network.

**Discussion:**

This is the first study to evaluate a certified trauma network within the German health care system using a unique combination of a quantitative (prospective cohort study) and a qualitative (in-depth facilitator/barrier analysis) approach. The information generated by this project will be used in two ways. Firstly, within the region the results of the study will help to optimize the pre-hospital and clinical management of polytrauma patients. Secondly, on a nationwide scale, influential decision-making bodies, such as the Ministries of Health, the Hospital Associations, sickness funds, insurance companies and professional societies, will be addressed. The results will not only be applicable to the region of Eastern Bavaria, but also in most other parts of Germany with a comparable infrastructure.

**Trial registration:**

VfD_Polyqualy_12_001978, 10.Jan.2013; German Clinical Trials Register DRKS00010039, 18.02.2016.

## Background

To date, chronic diseases have primarily been investigated in the context of health services research. One of the main reasons for this may be the wide availability of accessible data in the elective case situation. Acute care situations are much more challenging in terms of study management and data acquisition. Therefore this important segment of health care is definitely under-researched. This fact represents a striking contrast to the enormous amount of health care costs that are spent in acute and emergency care settings. Of particular importance is major multiple trauma (used synonymously with the term “polytrauma”) which causes higher socioeconomic burden than oncological and cardiovascular diseases [1, 2]. Consequently, the World Health Organization (WHO) has identified trauma as a key issue in future health care [3].

### Current state of research

The German Trauma Society (Deutsche Gesellschaft für Unfallchirurgie, DGU) started a nationwide multicentre study based on voluntary participation of trauma centres in 1993. This registry data collection currently contains some 160.000 cases with over 130 single items per patient until December 2013. The aim of this trauma registry was to analyse the performance of individual trauma centres, including the pre-hospital management, the clinical care setting, and outcome data. The main results of the Trauma Register DGU® [4] were published and served as the empirical and conceptual basis for the “White Book of the Severely Injured Patient” (2nd ed, 2012, [5]).

The White Book delineated the creation of a nationwide system of regional trauma networks. Similar to the American trauma system, a ranking of trauma facilities was introduced where all participating hospitals were classified into basic, (“Lokales Traumazentrum”, comparable to US level III), standard (“Regionales Traumazentrum”, comparable to US level II), and maximum (“Überregionales Traumazentrum”, comparable to US level I) care facilities. Strict rules for patient transfer were introduced with the aim to "get the right patient at the right time to the right hospital". According to the White Book the maximum transportation time for a major trauma patient from the scene should not exceed 30 minutes. The patient has to be transported to the next available standard or maximum care facility. If this time interval cannot be adhered to (either by ground or air transportation), the nearest basic trauma facility has to initially stabilize the patient and then transfer him/her as soon as possible to the next higher level of care institution. All hospitals within a region were audited and the network was not certified until an agreement on cooperation and uniform patient documentation was signed and the German S3 guideline on polytrauma care [6] has been implemented.

The effects of this major innovation in the German health care system cannot be predicted. Quite generally, it remains unclear whether trauma networks indeed improve the quality of care. More recently, trauma networks or trauma systems have been established in a number of different countries. Thus far, the reports on the results on an international level have been controversial. The Major Trauma Outcome Study in the USA, a trauma registry with more than 150.000 patients [7] has demonstrated the superiority of treatment of multiple injured patients in dedicated trauma centres [8]. In a Dutch study [9], the introduction of a regional trauma system reduced mortality and changed admission rates for all types of trauma. Other reports from the United Kingdom and from Switzerland could not show any improvement for mortality [10, 11]. The authors reached different conclusions in their respective health care settings due to the difference in the health care systems.

Based on these various philosophies the design of trauma centres differs greatly between countries with respect to size and catchment area (e.g. North America: centralization into a few maximum care facilities, Germany: decentralized health care system with many small to medium-sized facilities). Therefore it is difficult to apply the results of foreign studies to the German situation. Improving the quality of care also includes a profound understanding of care processes [12], which is especially true for the treatment of polytrauma patients in the acute period, due to the critical timeframe and the multidisciplinary co-operation required [13]. The “blueprint” is a quality management tool derived from the service industry, which structures and visualizes complex, customer-centred service processes and helps identify critical points (“moments of truth”) along the service process and within the interaction of different stakeholders [14, 15]. The blueprint method has been successfully transferred to patient-centred health care processes by some authors, e.g. with regard to mammography performance or outpatient care of hypertension [16, 17]. The method has not yet been applied to the acute care situation.

### Aim of the study

The aim of the present project is to evaluate the performance of the first certified regional trauma network in Germany, the Trauma Network Eastern Bavaria (TNO). In order to assess *qual*it*y* of care for *poly*trauma (*POLYQUALY*) the following specific research questions will be addressed:Do standard and maximum care facilities produce comparable (risk-adjusted) levels of patient outcome?Does network formation like the TNO outperform reference data provided by the German Trauma Register DGU^®^ 2008?Does TNO comply with selected benchmarks derived from the S3 practice guideline?What barriers and facilitators in the process of delivering health care to major trauma patients can be identified? How can these factors explain the results in patient outcome?

We hypothesize that the quality of care and therefore the outcome will be equal in hospitals with standard care in comparison to hospitals with maximum care facilities in a region if all hospitals are organized into a network structure that allows mutual support including the use of latest technologies such as telemedicine consultation. Furthermore, we hypothesize that TNO outperforms German Trauma Register DGU^®^ 2008 reference data and that the quality of care in the standard and maximum care facilities of TNO complies with guideline-derived benchmarks. In case our hypotheses hold true the qualitative barriers and facilitators analysis will be able to explain what the driving forces were that made this favorable results possible. In case the study results contradict our hypotheses the barriers and facilitators analysis can explain the hindering forces and may show ways how to improve the health care situation in the region.

The present project will also consider gender aspects. The majority of trauma patients (about 70 %) are male. In this study males and females will be enrolled according to the actual incidence of trauma events. After major trauma, quality of life differs between genders. Women have a 2.5 fold greater risk than men for developing psychological problems following major trauma and intensive care treatment (post-traumatic stress disorder, PTSD) [18, 19]. In order to address these gender-specific differences, quality of life outcomes will be compared between males and females.

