**Fig. 1 Fig1:**
[figure not shown]
Study design

The *prospective multicentre study* will (a) compare two cohorts of major trauma patients, those treated in maximum care facilities vs. those treated in standard care facilities, (b) compare results of the two cohorts with historical controls derived from the German Trauma Register DGU^®^ 2008 reference data and (c) compare results of the two cohorts with benchmarks including 5 outcome standards derived from the S3 guideline: risk adjusted morality (<15 %), door to CT-time (<20 min), ventilator free days (>22 days), ICU free days (>20 days), GOS (>80 % excellent and good).

The *qualitative part of the study* will (d) develop a service mapping tool (“blueprinting”) derived from quality management in the service industry in order to structure and visualize the care process for major trauma patients in the TNO, and (e) employ focus group discussions for identifying barriers and facilitators during the process, which can serve to explain why benchmarks are or are not met. This design allows for a comprehensive evaluation of TNO. In addition, the triangulation of methods provides for a profound understanding of the processes involved in acute major trauma care as well as the causal relationship between processes, structures and patient outcome. Whereas the quantitative study supplies data of patient outcome, and allows for comparisons between different health care standards plus the comparison of these results to benchmarks, the additional qualitative data provide an aid to interpretation and thus help in using the data for improvement of care processes and quality of care.

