### Study population and sampling

Patients will be recruited within the 25 hospitals that comprise TNO (Table 1). Inclusion criteria for the *prospective cohort study* are: major trauma ISS ≥ 16 (Injury Severity Score), treatment in any of the care facilities within the trauma network TNO, no age limitations. Exclusion criteria are ISS < 16, care outside TNO. Based on current register data it is expected that *n* = 1.100 patients will be assessed for eligibility and n = 800 be included and analyzed. For the *qualitative analysis* of barriers and facilitators, focus groups will be conducted with representatives of different professional groups involved in the TNO including emergency physicians, paramedics, dispatch centre staff, emergency room staff, trauma surgeons, rehabilitation staff and social workers. The focus group methodology can be transferred to other trauma networks and can be spread throughout Germany.

**Table 1 Tab1:** Trauma Network Eastern Bavaria / recruiting centres

Centre	Level of care
University Hospital Regensburg	Maximum Care Facility
Krankenhaus der Barmherzigen Brüder Regensburg	Maximum Care Facility
Klinikum Amberg	Standard Care Facility
Klinikum Eggenfelden	Standard Care Facility
Klinikum Deggendorf	Standard Care Facility
Klinikum Landshut-Achdorf	Standard Care Facility
Klinikum Neumarkt	Standard Care Facility
Klinikum Passau	Standard Care Facility
Klinikum Straubing	Standard Care Facility
Klinikum Weiden	Standard Care Facility
Krankenhaus Bogen	Basic Care Facility
Krankenhaus Burglengenfeld	Basic Care Facility
Krankenhaus Cham	Basic Care Facility
Krankenhaus Dingolfing	Basic Care Facility
Krankenhaus Freyung	Basic Care Facility
Krankenhaus Kelheim	Basic Care Facility
Krankenhaus Mallersdorf	Basic Care Facility
Krankenhaus Marktredwitz	Basic Care Facility
Krankenhaus St. Josef Regensburg	Basic Care Facility
Krankenhaus Schwandorf	Basic Care Facility
Krankenhaus Viechtach	Basic Care Facility
Krankenhaus Vilsbiburg	Basic Care Facility
Krankenhaus Vilshofen	Basic Care Facility
Krankenhaus Waldkirchen	Basic Care Facility
Krankenhaus Zwiesel	Basic Care Facility

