### Biostatistical concept / statistical analysis

*Prospective cohort study*: Statistical analyses of the prospective data will primarily dwell on descriptive statistics using counts, percentages, means/standard deviations, medians/interquartiles/ranges and confidence intervals. In order to interpret descriptive results they will be compared with secondary data from the Trauma Register DGU^®^ reference data bank 2008 and the benchmarks derived from the S3 guideline on major trauma. A logistic regression will be performed with 30 day mortality as the dependent variable and the ISS and TRISS scores as covariates. A p value of < 0.05 will be considered statistically significant. All other statistical tests will be chosen according to the scale level of the variable and the number of variables used in the model (t-test, Mann–Whitney U-Test, chi-squared test, risk-adjusted multivariable regression models) and will be performed in an explanatory manner, leaving alpha at < 0.05.

*Qualitative study*: Interview and focus group transcripts will be critically examined using thematic content analysis [23]. Themes will be identified using a grounded conceptualisation process [24]. Transcripts will be repeatedly read before and after coding to ensure proper categorisation of data. For the blueprint, the information on the health care process will be visualized as a two-dimensional picture: The horizontal axis represents the chronology of actions by the patient and the health care professional. The vertical axis distinguishes between different areas of actions, i.e. direct interactions between patient and professional, professional actions visible and invisible to the patient, support processes, and planning, managing and controlling activities [15, 17].

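### The plan hypothesises equal outcome in standard and maximum care facilities, but neither difference tests at p < 0.05 nor confidence intervals without a margin can establish comparability

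*Protocol article*

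**What the plan says.** In the section Aim of the study, the first research question is "Do standard and maximum care facilities produce comparable (risk-adjusted) levels of patient outcome". The hypothesis attached to it is that "the outcome will be equal in hospitals with standard care in comparison to hospitals with maximum care facilities", provided all hospitals work within the network. The text after Fig. 1 under Study design makes this comparison item (a) of the quantitative part: "those treated in maximum care facilities vs. those treated in standard care facilities".

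The section Biostatistical concept / statistical analysis says that the analyses "will primarily dwell on descriptive statistics using counts, percentages, means/standard deviations, medians/interquartiles/ranges and confidence intervals". It then names one model: "A logistic regression will be performed with 30 day mortality as the dependent variable and the ISS and TRISS scores as covariates". The criterion follows: "A p value of < 0.05 will be considered statistically significant". The remaining methods are "t-test, Mann–Whitney U-Test, chi-squared test, risk-adjusted multivariable regression models) and will be performed in an explanatory manner, leaving alpha at < 0.05".

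Under Study population and sampling, the sample size is an expectation from register data: 1,100 patients assessed and "n = 800 be included and analyzed". The article gives no margin, no equivalence or non-inferiority test, and no statement of what result would count as equal or comparable.

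**The concern.** The hypothesis and the inferential criterion point in different directions. The investigators want to show sameness, but in every listed test sameness is the null hypothesis. A p value below 0.05 can contradict the hypothesis; a p value above 0.05 leaves it neither supported nor refuted. The lower the precision, the more often a real difference ends as a non-significant result.

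The planned confidence intervals do not close the gap by themselves. An interval shows which differences the data exclude, but whether the remaining ones are small enough to be called comparable needs a margin.

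The first research question therefore cannot be answered affirmatively by the criteria the article sets. This matters beyond the region. The Discussion intends the results for health ministries, sickness funds and the professional society, and regards them as applicable to most parts of Germany with similar infrastructure. A claim of equal outcome resting on non-significance could influence how severely injured patients are distributed between levels of care.

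**Working it through.** **No stated calculation to reproduce.** The figure of 800 is a recruitment expectation. The article gives no power, effect size, margin or allocation from which it could be derived. What follows illustrates what 800 patients can show.

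**Inputs**
- Total of 800 patients (Study population and sampling). Assumption: all belong to the two cohorts.
- Mortality of 15%. Assumption: the only mortality figure available is the benchmark of below 15% under Study design, which is a target and not an expected rate.
- Split between cohorts: not stated. 400/400, 500/300 and 600/200 are shown, with either cohort as the larger.
- Two-sided alpha of 0.05. Assumption: sidedness is not stated.
- No risk adjustment and no clustering by hospital.

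**Step 1: precision.** With both cohorts at 15%, SE = sqrt[0.15 × 0.85 × (1/n1 + 1/n2)] and the half-width is 1.96 × SE.

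| Split | SE | 95% CI half-width |
|---|---|---|
| 400/400 | 0.02525 | 4.9 points |
| 500/300 | 0.02608 | 5.1 points |
| 600/200 | 0.02915 | 5.7 points |

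**Step 2: chance of a non-significant result when 15% (maximum care) versus 20% (standard care) is true.** This is 1 − Φ[(0.05 − 1.96 × SE0)/SE1], where SE0 uses the pooled rate and SE1 the two separate rates.

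| Maximum / standard | SE0 | SE1 | Non-significant |
|---|---|---|---|
| 400 / 400 | 0.02687 | 0.02681 | 54% |
| 500 / 300 | 0.02735 | 0.02808 | 55% |
| 300 / 500 | 0.02813 | 0.02729 | 57% |
| 600 / 200 | 0.03012 | 0.03182 | 61% |
| 200 / 600 | 0.03187 | 0.03007 | 66% |

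Using SE1 throughout (unpooled) keeps the results between 54% and 65%.

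**Step 3: other differences, same method.** For 15% versus 18%, the result is non-significant in 79–85% of studies. For 15% versus 25%, it is non-significant in about 5–16%, so an excess of 10 points would be detected in about 84–95%.

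**Step 4: sensitivity to the assumed rate.** Taking the lower rate anywhere from 10% to 20%, with splits from 400/400 to 560/240 and maximum care the larger cohort, a 5-point difference is missed in about 43–65% of studies.

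**Step 5: what a margin would demand.** Non-inferiority power with true equality at 15%, one-sided 2.5%, is Φ(margin/SE − 1.96).

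| Margin | 400/400 | 600/200 |
|---|---|---|
| 5 points | Φ(1.980 − 1.96) = 51% | Φ(1.715 − 1.96) = 40% |
| 7.5 points | Φ(2.970 − 1.96) = 84% | Φ(2.573 − 1.96) = 73% |
| 10 points | Φ(3.960 − 1.96) = 98% | Φ(3.430 − 1.96) = 93% |

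Equivalence, with the whole 95% interval inside the margin on both sides, is stricter: power is 2Φ(margin/SE − 1.96) − 1. At 400/400 this is about 2% for 5 points, 69% for 7.5 and 95% for 10.

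**The case against.** The strongest reply is that the plan is not a testing plan. It puts description with confidence intervals first and labels the other tests as explanatory. Level of care is not even named among the covariates of the one specified model, so it is hard to say that a decision rule for this hypothesis has been fixed at all. Much of this stands. A reader might infer that the plan will treat a non-significant p value as proof of equality, or that it contains a reversed decision rule. The documents support neither reading. No sentence says so, and the remark in the aims about what follows if the hypotheses are borne out concerns the use of the qualitative work and sets no statistical criterion. Nor is this hypothesis designated the main one; it is the first of several.

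The size of the problem should not be overdrawn either. Differences of 3 to 5 points would often be missed, but an excess of 10 points would usually be detected. The illustration places all 800 patients in the two cohorts, although 15 of the 25 hospitals are basic care facilities and patients treated anywhere in the network are eligible.

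A further reply is that a condensed article may leave a margin to a fuller document. That would answer a complaint of missing detail. It does not answer this point, because the article itself states both an equality hypothesis and a significance criterion, and the two do not fit. An analysis plan that implemented only the stated methods would still be unable to support the hypothesis.

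**Conclusion.** The concern holds as a mismatch between two things the article states: a hypothesis of equal outcome, and criteria (difference tests at p < 0.05, and confidence intervals without a margin) that cannot establish it. Misreading a non-significant result as equality is a risk that the text leaves open, not something it announces.

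Under the assumptions listed, the interval for the mortality difference would extend about 5 to 6 points either side of the estimate, and a true difference of 5 points would go undetected in somewhat more than half to about two thirds of studies. These figures are illustrative. Fewer patients in the two cohorts would widen the interval. Clustering within 2 maximum and 8 standard care hospitals would generally do the same. The effect of risk adjustment cannot be quantified from the documents. The mismatch itself depends on none of these numbers.

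**What to change.** Choose one of two routes before the data are seen.

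1. **Make comparability testable.** Restate the first hypothesis as equivalence, or as non-inferiority of standard to maximum care. Give a justified margin for the risk-adjusted 30-day mortality difference (standard minus maximum), and name level of care as the exposure term in the model. Conclude that outcomes are comparable only if the 95% confidence interval lies within the margin or, for non-inferiority, if its upper limit does. State what the expected number of patients in the two cohorts can support at that margin.
2. **Present the comparison as estimation only.** Report the risk-adjusted difference with its 95% interval and the largest difference not excluded, and make no claim of equality. This fits the descriptive emphasis already in the plan.

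If the first route is taken and the interval does not lie within the margin, report the result as under the second.

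Neither route needs new data. The cost is that comparable outcome becomes harder to claim. Under the same assumptions, non-inferiority power is 40–51% at a 5-point margin and 73–84% at 7.5 points, so a tight margin may leave the question open with the patients available. The margin should be justified clinically and not chosen to suit the sample size.
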